**Methods/Design:**

The CAN Stop study is a four-armed randomized wait-list controlled trial. The four arms are needed for the different help system settings, in which the CAN Stop training programme is evaluated: (a) the drug addiction aid and youth welfare system, (b) the out-patient medical system, (c) the in-patient medical system and (d) prisons for juvenile offenders. Data are collected at three points, before and after the training or a treatment as usual, and six months after the end of either intervention.

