
## Methods/Design

### Study Design and Setting

The CAN Stop study is a four-armed randomized wait-list controlled trial. Following Zwarenstein et al.'s [23] theoretical continuum of evaluation trials, on which rather "experimental", explanatory efficacy-oriented trials form the one end, and naturalistic, pragmatic effectiveness-oriented trials form the other end, this study tends towards the latter, pragmatic end. Developers were more interested in the real-life utility of the CAN Stop group training within the described four different contexts with their aforementioned specificities.

Data will be gathered at three points: before the group training (pre), after the group training (post; 3 months after pre) and at a follow-up (6 months after post). Modes of data retrieval vary from face-to-face interviews and questionnaires (pre), to questionnaires only (post) and telephone interviews and questionnaires (follow-up). Group comparisons will be made to check for the group training's effectiveness.

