In a first attempt to identify suitable cooperation partners, we systematically scanned comprehensive help provision and therapy guides of Northern and Eastern Germany as well as the Internet for institutions. All identified institutions were then invited to participate at the study with an information letter and asked to fax back an attached reply form together with a questionnaire about structural and work details of the institution, such as number of incoming young cannabis users in the targeted age range and number of staff. Prior to this, a target number of cooperation partners needed to gather the subjects was calculated on the basis of a power calculation, an estimated attrition rate of 50% and under the premise that CAN Stop training groups should be composed of six to ten group participants. If feedback was not given within six weeks after letters were sent out, a study group member called to check back with the institution. An exception from this procedure was made within the setting of juvenile prisons: because their total number was rather low, their staffs were contacted directly via phone calls. The response rate varied between different settings between 57% in juvenile prisons, 10% in in-patient medical clinics, 5% in out-patient medical clinics and 5% in the youth welfare and drug addiction aid. If institutions signalled to be in contact with young cannabis users in their daily routines and were interested in study participatioin, a study group member gave a presentation of the project and invited institutions to participate at the study. In sum, we could aquire a total of 11 cooperation partners within the youth welfare and drug addiction aid, 9 cooperation partners of the out-patient medical system, 8 cooperation partners of the in-patient medical system and 3 participating prisons for juvenile offenders. Participating cooperation partners were randomly assigned to perform the CAN Stop intervention plus their usual treatment as an intervention group or to provide for control group subjects, who received the cooperation partner's previously installed treatment as usual (TAU). As for other treatments, provided by the different institutions (besides CAN Stop), cooperation partners differed in their usually provided routines depending on their specific setting. While most prisons indicated, other kinds of therapy besides CAN Stop were rather limited and merely consisted of counselling talks or conceptual work within the organizational framework of the prison, the in-patient medical system's cooperation partners of course provided many other facets of treatment - to mention both extremes of this varying continuum. Institutions, which indicated they were already participating in other structured programmes similar to CAN Stop were excluded from the study in order not to compare CAN Stop with eventually competing studies (e.g. FrED, see above).

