
Recruitment for subjects was performed by cooperation partners within their daily work routines. In addition, the study group provided for flyers, which gave information on the study, its objectives and the group training to recruit participants. Young cannabis users interested in the programme were asked to contact a centralized telephone hotline installed by the study group to provide for a first check-up of inclusion criteria, to inform about the study and then to randomly allocate subjects to wait list control groups or to intervention groups in respective institutions. Young cannabis users in prisons are exempted from this procedure, because a random allocation of prisoners is not possible: the juidical allocation of young offenders into the prisons will decide about whether they are selected into a prison performing an intervention or a control group, their inclusion criteria are checked in in-take talks. Inclusion criteria were (1) the participants' age between 14 and 21 years, (2) a cannabis consume, which is deemed problematic by the young cannabis user or significant persons in his or her context (e.g. parents, teachers) (3) the participant's willingness to at least think over previous consumption patterns and to participate at a group dealing with the topic and (4) the informed consent of participants and in the case of underage participants the informed consent of a parent or official guardian. Young cannabis users were excluded from the study when they showed acute symptoms of psychosis or suicidality. Both of these exclusion criteria were checked via standardized screening questions at the beginning of the face-to-face take-in talks at the respective cooperation partner's institutions. Young cannabis users were invited to participate at the study regardless of whether their access to cooperating institutions was initiated by the cannabis users themselves or whether pressure was exerted by e.g. school, employers or because of a judicial condition of probation, however, this is documented and will be integrated into outcome analyses.

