### Ethical considerations

All procedures are in concordance with the ethics committee of the Chamber of Physicians in all federal states of Germany, in which the CAN Stop study takes place. All participants of the study and - in the case of underage young cannabis users - their parents or official guardians are informed about the study goals, procedures, analyses and data reporting prior to participation. Only data of participants who gave written consent will be used for analyses. All young cannabis users of the control group are offered the CAN Stop training after their data gathering is completed. In order to protect young cannabis users' identity to the study group personnel, videographies of CAN Stop training sessions will be made in a way that the camera is focused solely on the CAN Stop trainer - so only voices of young cannabis users are audible on videotapes.

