### Analysis

An intention-to-treat approach will be taken to analyze data. Comparisons will be made between intervention group and the TAU control group in the different settings using baseline controlled ANCOVAs with cannabis use and abstinence-oriented self-efficacy as dependent variable and cannabis use at t0 as covariate. We plan to perform nested analyses in order to handle the variance, which is shared between participants attending the same institution. There are no institutions, which offer more than one CAN Stop training group, so a further layer of nesting is not nescessary. We hypothesize that intervention groups show lower levels of cannabis use and higher levels of self-efficacy related to cannabis-abstinence after the intervention as compared to controls. To discover these effects, we calculated the needed sample size of n = 119, assuming a medium effect size of f = 0.25, given the power of the statistical test to .80 and setting the α-error on .05. Prior experience with the target group have shown that attrition rates among young cannabis users are rather high, so we calculated with an attrition rate of 50% when planning the number of nescessary participants at t0. With regard to further effects, we believe there are differences in the effectiveness of the training in the different settings. We hypothesize that the effect of the training (d) will be greater when less other interventions take place in the respective setting, that is, effects are bigger in juvenile prisons and out-patient institutions than in in-patient setting clinics.

Secondary analyses will be made to compare the clientele of the different settings. Here we assume that more aggravated and chronic cannabis users will be found in prisons and in-patient settings than in out-patient settings. As for the role forced access to the group (e.g. because of pressure from juidical institutions or teachers) plays, we believe no differences will be seen between participants, who indicated, they were attending the intervention group because of pressure from outside, as compared to participants, who decided to attend the group solely on their own accord. This is, because we assume the CAN Stop training itself is shaped in a way as to leave decisions about further consume open to participants, which inspires the internal motivation of all participants and therefore blurs differences regarding forced access to the training.

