## Discussion

In this paper, we describe the study design of an innovative training targeting young cannabis users in rather different settings, which are very differently organised but at the same time all share the goal to reduce their clientele's prior cannabis use. We are especially interested in how the different institutions will be able to implement the training, what the differences between their respective study participants are and how this is mirrored in the effect(s) of the training. A special difficulty of the study was to set up a study procedure which matches the different frameworks of the respective setting, starting at the professional background of the cooperation partners' staff, their legal and organizational background and their different interests.

Several difficulties may arise when it comes to the implementation of the study plan. First, it remains to be seen, whether it is suitable to use the centralized study telephone as a means to randomize young cannabis users into different institutions, especially, when they have already had contact to workers in one institution e.g. through a personal talk when handing out the study flyer, and they are assigned to another institution because the respective group is available only there. It remains to be seen, whether this potential switch marks a problem for recruitment, because other institutions are less easy to reach (e.g. with public transportation in rural areas) or an attachment has already been formed between one institution and a young cannabis user.

Another problem may arise through the referral of young cannabis users to other institutions by the centralized study hotline, because an institution, which may already have established a first contact to a young cannabis user, could "loose" a potential client to another, possibly competing institution and therefore may feel to loose money usually granted to them when treating the client. We hope that we can convince all cooperation partners that statistically, the possibility to "loose" clients through the centralized telephone hotline is as high as is the possibility to gain new clients because of the same centralized referral of study participants.

If it turns out, that the procedure with regard to the centralized telephone hotline poses a major threat to the recruitment of study participants, we will discuss to switch into a cluster randomized study design with cooperating institutions as randomized subjects.

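### The unit of randomisation is stated inconsistently, and on the only coherent reading exclusion screening and baseline follow allocation, so people lost in between leave the analysis called intention-to-treat

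*Protocol article*

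**What the plan says.** All statements are in the protocol article.

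- **Institutions (Recruitment of cooperation partners and young cannabis users).** "Participating cooperation partners were randomly assigned to perform the CAN Stop intervention plus their usual treatment as an intervention group"; the remaining institutions supply controls on treatment as usual (TAU). This is reported as completed. The partners number 11, 9, 8 and 3 (the 3 are prisons), 31 in all.
- **Individuals (same section).** After a first check of inclusion criteria, the hotline's task is "to randomly allocate subjects to wait list control groups or to intervention groups in respective institutions". Prisoners are exempt because they cannot be randomly allocated.
- **Fallback (Discussion).** If the hotline endangers recruitment, "we will discuss to switch into a cluster randomized study design with cooperating institutions as randomized subjects".
- **Label.** Study Design and Setting: "The CAN Stop study is a four-armed randomized wait-list controlled trial". The abstract explains: "The four arms are needed for the different help system settings, in which the CAN Stop training programme is evaluated". The Analysis section, however, states: "Comparisons will be made between intervention group and the TAU control group in the different settings".
- **Exclusion (Recruitment section).** For psychosis and suicidality: "Both of these exclusion criteria were checked via standardized screening questions at the beginning of the face-to-face take-in talks". These talks take place at the cooperating institution.
- **Blinding (Measures against bias).** Trainers who hand out the t0 and t1 questionnaires are unblinded. Trainers in control institutions learn the programme only after t1.
- **Analysis set.** The Analysis section promises an intention-to-treat approach, with cannabis use at t0 as covariate. Ethical considerations adds: "Only data of participants who gave written consent will be used for analyses".

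**The concern.** A reader cannot tell from the text what was randomised. If institutions have already been randomised, a cluster element is part of the present design and not only a fallback. If individuals are randomised, the document should say what the assignment of institutions contributes. The word arms adds to the confusion, because nobody is randomised to a setting.

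The order of events matters more. Intention-to-treat protects a comparison by following everyone from the moment of allocation. Here exclusion and baseline come after that moment, at a site that delivers only one condition and knows which. If the two conditions lose different kinds of people before t0, the groups entering the ANCOVA are no longer those that the hotline formed, and the result would still carry the intention-to-treat label.

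**Working it through.** **Step 1. Unit of randomisation, side by side**

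| Place | Unit randomised | Status |
|---|---|---|
| Recruitment section, on partners | Institution | Done |
| Recruitment section, on subjects | Individual, by hotline; prisons exempt | Current procedure |
| Discussion | Institution | Possible later switch |

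The first and third rows conflict unless something is added. The Discussion supplies it by describing the hotline as randomising users into different institutions. So institutions are first given a condition, and individuals are then randomised to an institution. On this reading the switch would remove the second stage and leave institutions as the only randomised unit. In the 3 prisons the second stage never existed. The article does not set this out in one place.

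**Step 2. Number of arms.** Two conditions (CAN Stop plus usual treatment, and TAU) are compared within four settings. The settings are strata.

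**Step 3. Order of events outside prisons**

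1. The hotline makes a first check of inclusion criteria.
2. The hotline allocates the person to an institution, and so to a condition.
3. A take-in talk at that institution begins with the psychosis and suicidality screen.
4. The t0 questionnaires are handed out by unblinded trainers.
5. The ANCOVA adjusts for t0 cannabis use.

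Someone lost at step 3, or before step 4, has no t0 value and cannot enter step 5 as described. In prisons there is no step 2: inclusion is checked at intake, in a prison whose condition is already set.

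**Step 4. Do the stated safeguards reach this gap?**

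- The nested analysis deals with variance shared within an institution, not with selection.
- The drop-out models are not said to cover people lost before t0.
- Blinding of the telephone interviewers protects t2 only.
- The 50% attrition allowance is applied in planning how many are needed at t0, so it concerns loss after t0.

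**Step 5. Possible size.** The plan gives no figure for losses between allocation and t0, so there is nothing to reproduce, and the inputs below are assumptions. Let a fraction p of one arm be lost before t0, with later use lying δ SD above the mean of everyone allocated to that arm. Let the other arm lose nobody. The mean of those remaining falls by p × δ / (1 − p).

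- p = 0.05, δ = 0.5: 0.05 × 0.5 / 0.95 = 0.026, about 0.03 SD
- p = 0.10, δ = 1: 0.10 × 1 / 0.90 = 0.111, about 0.11 SD

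The planned effect is f = 0.25, which for two equal groups is d = 2 × 0.25 = 0.5. The shifts are 0.026 / 0.5 = 5% and 0.111 / 0.5 = 22% of it, before baseline adjustment, which would reduce them. Loss of heavier users from the intervention arm would flatter the programme. The same loss from the control arm would hide an effect. Equal losses of the same kind in both arms would cancel.

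**The case against.** The strongest reply is that the two-stage design is coherent and the fault is one of wording. That largely stands for the unit of randomisation: the statements can be joined, but the reader has to do the joining, and the Discussion still presents randomisation of institutions as something new.

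On selection, four points deserve weight.

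- The hotline checks inclusion criteria before it allocates, so only the exclusion screen and t0 come afterwards. That is correct.
- The screening questions are standardised, which limits discretion.
- The consent sentence is an ethical safeguard rather than a definition of the analysis set, and the timing of written consent is not stated. Whether refusals occur after allocation is therefore open.
- What participants are told at allocation is not stated. Knowledge of the condition is documented for staff only.

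These points make arm-differential selection a risk inferred from the sequence, not a documented event. They do not close the gap, because loss before t0 can also come from non-attendance. The Discussion itself expects difficulty when people are sent to an institution that is harder to reach, or away from one they already know.

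A reader might infer more than the documents support:

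- **That clustering is ignored.** The Analysis section plans nested analyses by institution.
- **That participants recruited before and after a switch would be pooled without regard to how they were allocated.** The text promises only a discussion of a switch and describes no such pooling.
- **That differences between settings would be presented as randomised comparisons.** The Analysis section compares conditions within settings, the Background expects different clientele across them, and the prison exemption is stated openly.

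**Conclusion.** The point holds in two parts. First, the abstract, the Study Design and Setting section, the Recruitment section and the Discussion do not agree on what was randomised, and four-armed names settings in a comparison of two conditions. Second, on the only coherent reading, people outside prisons who are excluded or lost between hotline allocation and t0 drop out of an analysis called intention-to-treat, after contact with staff who know the condition.

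The size of the second part is unknown. The range of 0.03 to 0.11 SD, or 5% to 22% of d = 0.5, rests entirely on assumed losses of 5% to 10% in one arm only, lying 0.5 to 1 SD above that arm's mean, without baseline adjustment. It shows that the effect could be negligible or noticeable. The documents do not show that bias will occur, and nothing here means that the comparison outside prisons is not randomised.

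**What to change.** 1. **State the design once, in the same words throughout:** two conditions within four settings, institutions assigned to a condition, individuals allocated to institutions by the hotline, prisons not individually randomised. Drop four-armed. Describe the possible switch as removal of the individual stage.
2. **Define the intention-to-treat population from hotline allocation.** Log everyone allocated and report by arm how many were screened out, did not consent or were lost before t0. Where feasible, complete eligibility screening and consent before the hotline allocates. Merely delaying disclosure of the allocation would not work as the plan stands, because the allocation decides which institution does the screening.
3. **Record how each participant was allocated** (hotline, institution only, prison) and repeat the main analysis in hotline-randomised participants only. Describe results from the 3 prisons as not individually randomised. A fixed effect for allocation mode is no substitute: it removes a mean difference between modes, not selection that differs by arm within a mode.

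The cost is revised wording, an allocation log, one recorded variable and one sensitivity analysis with lower precision. Screening before allocation, where it can be arranged, adds some hotline work.

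### The prison setting is at best three randomised clusters, so its training effect cannot be separated from prison differences, yet it is labelled, compared and ranked like the other settings

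*Protocol article*

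**What the plan says.** All places are in the protocol article.

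- **Design label.** Study Design and Setting: "The CAN Stop study is a four-armed randomized wait-list controlled trial". The abstract uses the same label and lists the settings, the last two being "c) the in-patient medical system and (d) prisons for juvenile offenders". Neither place qualifies the label for prisons.
- **Number of prisons.** Recruitment section: "3 participating prisons for juvenile offenders", beside 11, 9 and 8 institutions in the other three settings.
- **Institution-level allocation.** Same section: "Participating cooperation partners were randomly assigned to perform the CAN Stop intervention plus their usual treatment as an intervention group", or else to supply control participants under treatment as usual (TAU). No exception is stated for prisons.
- **Individual allocation.** Callers to the hotline are randomly allocated. Prisoners are exempt "because a random allocation of prisoners is not possible: the juidical allocation of young offenders into the prisons will decide" the matter, namely "whether they are selected into a prison performing an intervention or a control group". Each prison therefore carries one condition only.
- **Analysis.** Baseline-adjusted ANCOVAs compare intervention with TAU in the different settings, with nesting for institution. The section then predicts that "effects are bigger in juvenile prisons and out-patient institutions than in in-patient setting clinics".

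Neither Measures against bias nor the Discussion comes back to the prison allocation.

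**The concern.** With three prisons and one condition per prison, the only split that keeps both conditions is two against one. Whatever distinguishes the lone prison (regime, access to drugs, the offenders the courts send there) is then part of the estimated training effect. Measuring more prisoners does not change that.

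This matters because comparing effectiveness across settings is one of the stated goals in the Background, which also says that no manualised or evidence-based prison programme is known to the authors. A prison result from this trial is therefore likely to be noticed. Under the unqualified label it could be read as evidence of the same standing as that from the hotline-randomised settings. The predicted ranking of settings also depends on a prison contrast that the design cannot deliver.

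**Working it through.** **The plan's own figure.** The Analysis section gives n = 119 for f = 0.25, power 0.80 and alpha 0.05. It gives no figure for prisons. A two-group F test with these inputs needs 128. An ANCOVA with an unstated baseline correlation of 0.20 to 0.30 needs 122 to 116, which would cover 119. Nothing below rests on this; only the effect size is carried over, as d = 2f = 0.5 for two equal groups.

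**Inputs**

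- Prisons: 3, hence 2 against 1 (Recruitment section).
- Participants per prison, m: not stated. Training groups have 6 to 10 members, and the planned attrition of 50% would leave 3 to 5. I use m = 3 to 10 as an assumed range.
- ICC between prisons: not stated. Assumed range 0 to 0.10.

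**Step 1: what the contrast estimates.** Write a prison mean as μ + τz + u + e, with τ the training effect, z the condition, u the prison's own deviation and e the average of individual errors. The two-against-one contrast estimates τ plus the difference between the mean u of two prisons and the u of the third. With total variance 1, the standard deviation of that unwanted part is √(1.5 × ICC):

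| ICC | SD of the prison part |
|---|---|
| 0.01 | √0.015 = 0.12 |
| 0.05 | √0.075 = 0.27 |
| 0.10 | √0.15 = 0.39 |

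The effect sought is 0.5. No value of m enters this line.

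**Step 2: prisons analysed alone.** Variance of a prison mean: v = ICC + (1 − ICC)/m. SE = √(v × (1/2 + 1)). Degrees of freedom: 3 − 2 = 1, so the two-sided 5% critical t is 12.71. Power comes from the noncentral t with noncentrality 0.5/SE.

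| m | ICC | SE | Power, 1 df |
|---|---|---|---|
| 3 | 0 | 0.707 | 6.2% |
| 3 | 0.10 | 0.775 | 6.0% |
| 6 | 0 | 0.500 | 7.3% |
| 6 | 0.10 | 0.612 | 6.6% |
| 10 | 0 | 0.387 | 8.7% |
| 10 | 0.10 | 0.534 | 7.0% |
| 40 | 0 | 0.194 | 16.1% |
| 40 | 0.10 | 0.429 | 8.0% |

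With unlimited prisoners, v tends to the ICC, and power is still only about 25% at ICC 0.01 and 9% at ICC 0.10.

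**Step 3: borrowing variance from the other settings.** A nested model over 11 + 9 + 8 + 3 = 31 institutions with 4 × 2 = 8 setting-by-condition cells has about 31 − 8 = 23 institution-level df, if between-institution variance is the same in all settings. The critical t falls to 2.07. With the same SEs, power runs from 9.5% (m = 3, ICC 0.10) to 23.6% (m = 10, ICC 0), that is, roughly 10% to 24%. Step 1 is unchanged.

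**Step 4: if nesting were dropped for prisons.** The nominal 5% test would have a type I error of 2 × [1 − Φ(1.96/√(1 + (m − 1) × ICC))]. This is about 6% to 16% at m = 6 to 10 and ICC 0.01 to 0.10.

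**The case against.** The strongest defence has five parts.

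1. **The label is true at institution level.** The Recruitment section says institutions were randomly assigned and makes no exception for prisons. This stands: a reader might infer that calling the prison setting randomised is false, and the text does not support that. Cluster-randomised with three clusters is the accurate description. But random assignment of three units cannot be expected to balance prisons or inmates, and the label hides that the allocation unit differs from the hotline settings.
2. **Clustering is planned for.** A reader might infer an ANCOVA on individuals that ignores institutions. The Analysis section plans nested analyses, so Step 4 is a warning and not a description of the plan. Nesting still cannot separate the training from a lone prison.
3. **No pooled headline estimate is specified.** This is correct. The Background says the settings are evaluated separately, and n = 119 is not tied to a pooled or a per-setting test. That a pooled main result is contaminated by prisons is therefore conditional on one being made.
4. **The ranking is not called confirmatory.** Also correct. It is introduced as a belief about further effects, with no test or alpha assigned.
5. **Some figures that suggest themselves are not forced.** A smallest randomisation p-value of 1/3 assumes a fixed 2:1 split; if the split was itself random there are 6 assignments and the floor is 1/6. Neither reaches 0.05. A total of 9 to 15 completers (3 × 6 to 10 × 0.5) assumes one group-sized sample in every prison, whereas the limit concerns training groups and not TAU participants. The critical t of 12.7 applies only to prisons analysed alone. With 40 per prison and borrowed variance, power would be 20% to 70% over ICC 0.10 to 0, so low power is not the decisive argument; the confounding is.

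The exemption is also stated openly, with its legal reason. What is missing is any consequence drawn from it for the label, the comparison or the prediction.

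**Conclusion.** The point holds for the prison setting and for the between-setting prediction that uses it. The design supports no causal statement about the training in prisons, because at least one condition is a single prison; that follows from the count of three and needs no assumed figure. The supporting sizes are power of about 6% to 9% for prisons alone and roughly 10% to 24% with borrowed variance, both for d = 0.5, m = 3 to 10 and an assumed ICC of 0 to 0.10.

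A reader might go further and say that any prison p-value would mostly reflect prison differences. That is not supported over the assumed range: at m = 6 and ICC 0.10, the between-prison share of the variance of a prison mean is 0.10/(0.10 + 0.90/6) = 40%, and it is smaller at lower ICC. The exact statement is that the two sources cannot be separated. The other 28 institutions are not affected by this point.

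**What to change.** - **Abstract, Study Design and Setting, and Recruitment section:** state that individuals are randomised in three settings, and that prisons are assigned as whole institutions (three clusters, no individual randomisation).
- **Analysis section, prison results:** report them per prison as descriptive estimates, without a significance test or causal claim.
- **Analysis section, ranking of settings:** remove prisons from any tested comparison of effect size between settings. The expectation may stay as a descriptive remark.
- **Analysis section, pooling:** if a pooled estimate is made, base it on the hotline-randomised settings (28 of 31 institutions) and show the version including prisons as a sensitivity analysis.
- **Discussion:** name the prison confounding among the weaknesses.

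The cost is mainly wording. Any pooled estimate loses 3 of 31 institutions (9.7%); the share of participants is not known from the article. The trial also gives up a formal test of effectiveness in prisons, which three prisons cannot usefully provide.
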